### Sample Size Determination

To make sure the sample size is big enough to test the hypotheses, a small to medium effect size (Cohen *d*=0.33) is used based on prior research [11], power set at 0.80, and α set at .05. A final sample size of 438 (146 per arm) is required. With reference to the attrition rate of our previous studies in a school setting, which is less than 20%, there is a requirement to recruit 549 participants at the baseline (183 per arm).

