Fifth, to ensure the intervention will be conducted in a standardized surrounding, the intervention will be conducted in activity rooms in each school. Around 12 to 20 student participants with parental consent will be invited to participate in the intervention as a group under the support and administration of well-trained research assistants. We also monitor the time spent on each part of the presentation with computing programming techniques. Participants with too long and too short duration time (usually above 2 SDs) in 1 section will be double-checked on their participation effectiveness, and biased data will be eliminated.

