### Data Collection and Management

Assessments will be conducted by a blinded researcher trained in using the instruments. Self-rated scales will be completed by the participants under guidance. All the measures have been pilot-tested, and the questionnaires take about 20 minutes to be completed. Two attention-checking items will be included in the surveys of each time point for careless responding screening (eg, “Please choose *Strongly Agree* for this item”). Only those who answer both attention-checking items correctly each time will be included in the final data analysis [23]. As the literature has shown motivation playing pivotal roles in people’s behavioral change, we will also add 2 items at the beginning of the survey at baseline to assess participation motivation of our participants with a 6-point Likert scale, asking about their motivation to participate in this program and improve their emotion regulation ability, respectively.

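### The inflation from 438 to 549 allows for attrition only, while the plan's own data-quality exclusions also remove students from the final analysis

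*Protocol article*

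**What the plan says.** Sample Size Determination sets the assumptions as "a small to medium effect size (Cohen *d*=0.33) is used based on prior research [11], power set at 0.80, and α set at .05" and concludes: "A final sample size of 438 (146 per arm) is required". It then inflates for one kind of loss: "With reference to the attrition rate of our previous studies in a school setting, which is less than 20" per cent. On that basis, "there is a requirement to recruit 549 participants at the baseline (183 per arm").

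Two later parts of the Methods describe other losses.

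- **Attention checks** (Data Collection and Management): "Two attention-checking items will be included in the surveys of each time point for careless responding screening", followed by the rule "Only those who answer both attention-checking items correctly each time will be included in the final data analysis". Research Design sets three assessments: baseline, 2 weeks and 8 weeks.
- **Session time** (Implementation Strategies, fifth strategy): students whose time on a section is unusually long or short, usually beyond 2 SDs, "will be double-checked on their participation effectiveness, and biased data will be eliminated".

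Neither part gives an expected rate. Nothing says that the 20% already covers these exclusions. The Data Analysis section states intention-to-treat, with reference to missing data.

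**The concern.** The sample size section and the attention-check rule both speak of what is final: one of the final sample, the other of the final data analysis. They are not the same set. The first is recruitment less attrition. The second is recruitment less attrition less everyone who fails a check. If the allowance is used up by attrition, the number analysed under the plan's own rules falls below the number called required, and the 80% power attached to 438 then belongs to a larger set than the one to be analysed.

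This concerns the planning number and is separate from any bias that such exclusions cause after randomisation. It would hold even if failures were purely random.

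**Working it through.** **Inputs from Sample Size Determination:** d = 0.33, power 0.80, α = .05 (taken as two-sided, since one-sided gives 114 per arm and does not match), three equal arms, attrition 20%. **Not given anywhere:** the rate of attention-check failure or of session-time elimination.

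**1. Reproduce the plan's figures.** A two-sample t-test with these inputs needs 145.1 per arm, rounded up to 146; 146 × 3 = 438. Inflation: 146 / (1 − 0.20) = 182.5, rounded up to 183; 183 × 3 = 549. Both stated figures are confirmed.

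**2. Spare capacity at the planned attrition.** 549 × 0.80 = 439.2, and 439.2 − 438 = 1.2 students over all three arms, or 0.4 per arm.

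**3. Break-even exclusion.** Let a be attrition and f the share of retained students excluded. The final sample stays at 438 or more only if f ≤ 1 − 438 / [549 × (1 − a)].

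| Attrition a | Retained, 549 × (1 − a) | Break-even f |
|---|---|---|
| 20% | 439.2 | 0.27% |
| 15% | 466.65 | 6.1% |
| 10% | 494.1 | 11.4% |

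At 20% attrition, two failures in the whole trial are enough to fall below 438.

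**4. Illustration of size at 20% attrition.** The rates here are assumptions. Suppose 5% fail at a wave.

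- If the same students fail at every wave, f = 5%: 439.2 × 0.95 = 417, about 139 per arm.
- If failures are independent over three waves, f = 1 − 0.95³ = 14.3%: 439.2 × 0.95³ = 377, about 125 per arm.

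| Total exclusion f | Analysed | Power at d = 0.33 | d detectable with 80% power |
|---|---|---|---|
| 0% | 439 | 80% | 0.33 |
| 5% | 417 | 78% | 0.34 |
| 14.3% | 377 | 74% | 0.355 |

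Power is from the two-sample t-test at α = .05 as if students were randomised individually. That isolates this one loss. It is not the power of the class-randomised design. Session-time elimination is left out because the text gives no basis for a rate.

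**The case against.** **The sums are correct.** This stands. 146, 183, 438 and 549 all reproduce, so a reader who inferred an arithmetic error would be wrong. The gap is in what the loss term covers.

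**20% is a ceiling.** This also stands. Earlier attrition is described as below 20%, so planning at 20% leaves slack of unknown size. With 10% attrition, 438 survives exclusions of up to 11.4%. A reader might infer that 438 and its 80% power are simply overstated, but the article does not establish that. It shows only that nothing is left over at the attrition from which 549 was derived.

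**The size is assumed.** A reader might take 377 analysed and 74% power as the expected result. That needs full 20% attrition, a 5% failure rate per wave and independence between waves, none of which is in the article. If the same students fail each time, the loss is about 2 percentage points of power.

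**The rules may remove less than they seem to.** The session-time rule begins with a check and then eliminates data, which need not mean whole students. The attention rule most naturally means passing at every wave, but a wave-by-wave reading is possible and would remove fewer. Past attrition might already include careless responders, though the article does not say so. The attention rule still carries the point on its own, because the margin at 20% attrition is about one student.

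**Intention-to-treat keeps everyone.** The Data Analysis section applies that principle to missing data, while the attention rule takes students out of the final analysis. If the intention is to keep them, the attention rule is the text that needs to change.

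**This belongs in the analysis plan.** An expected failure rate might well be left to it. But the loss allowance and the exclusion rule are both stated in the article, and they describe different sets.

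**Conclusion.** The point holds in a limited form. The 549 is built for attrition alone at its 20% upper bound, leaving 1.2 students spare, while a firm exclusion rule acts on the same final analysis and has no allowance. At that attrition, exclusion of more than 0.3% of retained students brings the sample below 438. Lower attrition could absorb the loss.

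If exclusions reached 5% to 14% at 20% attrition, the cost would be roughly 2 to 6 percentage points of power, ignoring clustering. Those rates are assumptions, so the actual shortfall, if any, cannot be computed from the article. The conclusion rests on reading the attention rule as excluding whole students and on past attrition not already counting them. It is a minor to moderate point.

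**What to change.** Either of two changes settles it.

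1. **Preferred.** Keep all randomised students in the primary intention-to-treat analysis, use the attention-check and session-time exclusions only in a sensitivity analysis, and state under Sample Size Determination that 438 applies to the full set. This also removes the tension with the intention-to-treat statement.
2. **If the exclusions stay in the primary analysis.** Restate the loss as attrition and exclusions combined, so that the analysable number is 549 × (1 − a) × (1 − f), and give the resulting number, power and detectable d. Take f from the team's earlier school studies or show a stated range. The pilot cannot supply it: it had 13 students aged 15 to 17, and no follow-up waves are described. If earlier attrition already counted careless responders, one clause saying so is enough.

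The cost is a sentence or two and, under the second option, a slightly less favourable stated power. No extra recruitment is asked for.

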### Participant Eligibility and Randomized Control Process

Eligible participants (aged 12-16 years) in grades 7-9 will be recruited from 6 secondary schools through cluster randomized sampling. The inclusion criteria will include (1) ages between 12 and 16 years, (2) Chinese youth who can read and write Chinese, (3) enough visual and auditory abilities to complete the intervention and assessment, and (4) ability to give assent to participate in the study.

Exclusion criteria will include (1) no parental consent; (2) inability to stay focused to complete the intervention, which is approximately 45 minutes; and (3) intellectual disability or severe illness or pain that would lead to significant bias in students’ health and mental health situation. Eligible participants will not be screened for their anxiety symptoms; thus, this study will comprehensively examine the efficacy of the interventions for students with mild, moderate, and severe levels of anxiety.

The school and student recruitment process will include the following steps. First, we will send research invitations to schools chosen randomly from the school list. Invitations will stop when 6 schools agree to participate. At least 3 classes in the same selected grade of each school will be randomly selected to join the study, and then the 3 selected classes will be randomized to the SIGMA condition, SSI-GP condition, and the active control condition by random numbers. All students in those classes will be invited to participate and the final participation depends on parental consent and students’ assent. Based on prior trials in local schools, about 60% of students are likely to agree to participate with parental consent. Thus, approximately 90 students will be recruited from each school.

After consenting, students will be asked to complete a battery of questionnaires (detailed below) via the Qualtrics survey system. The students in 1 class will be in the same intervention conditions. The interventions will be conducted separately for each group in the school activity rooms with sufficient computers or tablets and headphones. All intervention activities are self-administered and delivered in a web-based format. The principal investigator and well-trained research assistants will stay in the intervention rooms to provide guidance and help if needed. All groups in 1 school will be conducted concurrently or within 2 weeks to reduce the influence of the time factor.

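### Classes are allocated before students are invited, consented and measured at baseline, and no safeguard is described against knowing the arm at that stage

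*Protocol article*

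**What the plan says.** The section Participant Eligibility and Randomized Control Process presents recruitment as a sequence: "The school and student recruitment process will include the following steps". In the order given:

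1. Schools are invited until 6 agree.
2. At least 3 classes of one grade are selected at random in each school, "and then the 3 selected classes will be randomized to the SIGMA condition, SSI-GP condition, and the active control condition by random numbers".
3. "All students in those classes will be invited to participate and the final participation depends on parental consent" and the student's own assent. The expected uptake is that "about 60% of students are likely to agree to participate with parental consent".
4. "After consenting, students will be asked to complete a battery of questionnaires".

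Allocation therefore comes before invitation, consent and baseline. Research Design confirms that the class is the randomized unit and gives no other order. The Abstract says nothing about sequence. The CONSORT flow diagram (Figure 2) is not shown, so it could not be checked.

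The only blinding stated is under Data Collection and Management: "Assessments will be conducted by a blinded researcher trained in using the instruments". The same section says that the scales are self-rated and that two motivation items open the baseline survey. Motivation for change is the moderator in hypothesis 3 (Aims and Objectives).

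**The concern.** Randomizing classes balances classes. It does not balance the subset of students who agree to join after the class has its arm. If whoever issues the invitation, a teacher, a parent or a student knows or guesses the arm, the willingness to join can depend on it, and so can the answers to a self-rated baseline.

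Four features make this worth attention here:

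- About 40% of invited students are expected not to take part, so there is room for selection.
- With 6 schools and 3 classes each, there may be only about 6 classes per arm to average out differences in recruitment.
- One exclusion criterion, "inability to stay focused to complete the intervention, which is approximately 45 minutes", calls for judgement about individual students. The text does not say when it is applied. If it is applied at enrolment, the class already has its arm.
- Effect sizes are built on gain from baseline (Data Analysis), so a baseline score coloured by knowledge of the arm enters the estimate directly.

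Intention-to-treat keeps enrolled students in their arm. It cannot bring back students who never consented.

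**Working it through.** **Inputs from the Protocol article.** d = 0.33, power 0.80, alpha .05, 146 per arm analysed, attrition below 20%, 549 at baseline (Sample Size Determination); about 60% consent (Participant Eligibility and Randomized Control Process); effect sizes on gain from baseline (Data Analysis).

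**Assumed, because the documents give no value.** The dependence of consent on a prognostic trait in each arm, and the pre-post correlation r of GAD-7.

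**1. The plan's own figure.** A two-sided two-sample t-test with d = 0.33 and 80% power needs 145.1 per arm, rounded up to 146. Then 146 / 0.80 = 182.5, rounded up to 183, and 3 × 183 = 549. The plan's numbers reproduce.

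**2. Size of the exposure.** 549 / 0.60 = 915 students invited (305 per arm), and 915 − 549 = 366 not taking part.

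**3. Gap in an entry trait.** Let z be a standard normal trait such as anxiety or motivation, with consent probability expit(a + bz) and a set so that 60% consent overall. The mean of z among consenters is E[z · expit(a + bz)] / 0.60, which is approximately b × (1 − 0.60).

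| Consent slope b in one arm (0 in the other) | Approximation | Computed gap |
|---|---|---|
| 0.3 | 0.3 × 0.40 = 0.12 | 0.12 SD |
| 0.5 | 0.5 × 0.40 = 0.20 | 0.19 SD |

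If the slope and the consent rate are the same in both arms, the gap is 0, whatever the slope.

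A second model gives a similar range. If consent is a threshold on a latent willingness that correlates rho with the trait, the shift among consenters is rho × φ(z_p) / p. At p = 0.60, with rho of 0.1, 0.2 or 0.3 in one arm and 0 in the other, the gap is 0.06, 0.13 or 0.19 SD. With rho = 0.2 in both arms but consent of 65% against 55%, or 70% against 50%, it is 0.03 or 0.06 SD.

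**4. From entry gap to bias in the planned analysis.** Suppose the trait is baseline anxiety, the SDs at baseline and follow-up are equal, and there is no treatment effect. A baseline gap g leaves an expected follow-up gap of r × g, so the arms differ in change by (1 − r) × g. The arm that starts higher appears to improve more.

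| Entry gap g | r = 0.5 | r = 0.7 |
|---|---|---|
| 0.12 SD | 0.06 | 0.036 |
| 0.19 SD | 0.095 | 0.057 |

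The range is about 0.04 to 0.10 SD. For a trait such as motivation, the bias is the gap scaled by how strongly the trait relates to change. The documents give no value for that.

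**The case against.** The strongest reply is that the decisive link is not in the text. Recruiting after allocation biases the comparison only if the arm is known or guessed, and no section says that it is disclosed before consent or that invitations differ by arm. A single invitation process is described for all students in the selected classes. The article is condensed, Research Design commits the trial to CONSORT, and the full protocol may contain a masking rule.

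The design also lowers the risk. All three conditions are self-administered web sessions of about 45 minutes. The control is built to mirror the other two, and there is no waitlist arm. The arms sit in the same grade of the same school. A family that learned its class's arm would have less reason to decline than in a trial of treatment against nothing. Analysis of change removes most of an imbalance in baseline anxiety itself. Motivation is asked before the intervention, so it is affected only through the same unproven route.

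Most of this stands, and it limits the size of the point. It does not remove it. The article does more than leave out a detail: it fixes an order that creates the exposure and describes no protection at that stage. Similar active arms make selective consent less likely, not impossible. A change score does not correct for unmeasured differences in who joins, nor for a baseline answered in knowledge of the arm.

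**Conclusion.** The point holds as a matter of stated order: allocation, then invitation, consent and baseline, with no masking of the arm described at those steps. If the arm is known or guessed, the enrolled students and their self-rated baseline GAD-7 and motivation can differ by arm. Randomization of classes and intention-to-treat do not guard against this.

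The size is unknown. The entry gap runs from 0 (consent works alike in all arms) to about 0.12 to 0.19 SD under the assumed slopes. For baseline anxiety, the bias in change is then about 0.04 to 0.10 SD for r between 0.5 and 0.7. The slopes, the zero slope in the comparison arm and r are all assumptions.

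A reader might infer three stronger things that the documents do not support:

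- That the arm is in fact disclosed before consent. No section says so.
- That the bias could amount to a third to a half or more of the planned effect, by setting 0.12 to 0.19 beside 0.33. The first is a gap in an entry trait and the second is a treatment effect. Because the analysis uses change from baseline, they should not be compared directly.
- That 40% non-participation is itself a bias. If consent works the same way in every arm, it limits generalizability and leaves the comparison between arms intact.

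**What to change.** In the selected classes, obtain parental consent and student assent with identical materials and complete the baseline, including the motivation items. Only then draw or release the within-school allocation. If timetables require earlier allocation, conceal it from recruiters, school staff and families until the baseline closes. In either case, report consent rates by class and arm. If the full protocol already conceals the allocation, one sentence saying so in the recruitment steps would settle the point.

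The cost is small. Sample size, arms and interventions do not change. Rooms and sessions are scheduled slightly later, which fits the existing allowance for running a school's groups concurrently or within 2 weeks.

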### Implementation Content

#### SIGMA

The SIGMA intervention group will adapt the SSI-GP protocol in two ways: (1) by introducing the growth mindset of emotions rather than personality and (2) by providing an experiential process of negative emotion change. SIGMA also consists of five components: (1) an introduction to emotions and the brain for conveying a scientific understanding of emotion and growth mindset of negative emotions; (2) stories and testimonials from high school–aged youths who described their beliefs that people’s negative emotion states (eg, anxiety, depression, and stress) are malleable, and how these mindsets influence their coping with anxiety; (3) emotion changing experience induced by short videos; (4) common questions and misconceptions about growth mindset; and (5) self-persuasion writing exercises in which the participants write notes to younger students about the growth mindset of emotion. Table 1 presents the key elements of the interventions. For participants at each school who belong to the SIGMA group, we will randomly select half of them to give them booster messages with core intervention content every 2 weeks between the 2-week posttest and the 2-month follow-up survey, that is, a total of 5 weekly booster messages will be sent to half of the participants of the intervention group, which will help us determine the most effective way of implementing the intervention.

**Table 1 table1:** Intervention elements.

Intervention elements	SIGMA^a^ (45 minutes)	SSI-GP^b^ (45 minutes)	ST^c^ (45 minutes)
Science knowledge about neural plasticity of the brain	✓ Growth mindset of negative emotions	✓ Growth mindset of personality	Nil Science videos about emotions
Stories and testimonials from high school-aged youths	✓ Focused on emotion changing experience	✓ Focused on personality change	✓ Focused on emotion sharing
Experiential exercises	✓ Emotion coping strategies	Nil	Nil
Self-persuasion writing exercises	✓ Focused on the malleability of negative emotion	✓ Focused on the malleability of personality	✓ Focused on sharing emotion to close others

^a^SIGMA: single-session intervention of growth mindset on negative emotions.

^b^SSI-GP: single-session intervention growth mindset of personality.

^c^ST: support therapy.

A pilot test among 13 secondary students (ages from 15 to 17 years) was conducted to confirm the feasibility and acceptability of the intervention in a small sample of the targeted population. The intervention lasted around 45 minutes and could be finished in one school class session.

#### SSI-GP

SSI-GP intervention group will use the intervention protocol of project personality [20]. We will translate it into Chinese by 2 bilingual native English and Chinese speakers and make adaptations to the local education context. The key potent elements of SSI-GP consist of five components [15,21,22]: (1) an introduction to the brain about the potential of neuroplasticity and behavioral change; (2) written testimonials from older, high school–aged youths of their belief in change of personality; (3) additional vignettes written by older youths about how growth mindset of personality helped them succeed following setbacks; (4) overview of common questions and misconceptions about growth mindset; and (5) an exercise of writing notes to younger students about the malleability of people’s personality traits.

